**Sub-study B** is an observational, follow-up study of at least 100 pregnant women identified in sub-study A as being infected with *S. haematobium* (by egg microscopy and/or urine UCP-LF CAA test). *Schistosoma*-infected women will be randomised 3:1 (75:25) for immediate PZQ treatment during the pregnancy (single dose of 40 mg/kg) or delayed PZQ treatment after delivery (control group). The control group will not be treated during pregnancy (to monitor “natural” CAA level fluctuation in a participant if not treated), but 6 months after delivery. The primary objective is to determine the kinetics of CAA after treatment during pregnancy compared to the control group. The control group serves also as a safety control of PZQ administration to pregnant women and exposure of their offspring (s). Therefore, both groups (treatment and control) will be actively followed-up and urine will be collected on day 2, day 4 and day 6 after PZQ treatment and then once a week until both egg microscopy as well UCP-LF CAA assay become negative but no longer than 6 weeks after PZQ treatment. The secondary objective is to collect data on safety of PZQ during pregnancy. For details on the safety investigation, see below (treatment, adverse events and safety assessment).

**Sub-study C** will follow up infants born to mothers included in sub-study A and their mothers for a maximum of 24 months (*N* = 200). This is an observational, longitudinal study with the primary objective to determine the incidence of *S. haematobium* infection and age of first *S. haematobium* infection in infants. Therefore, after delivery, mother and her infant will be asked to provide urine every 3 months until the UCP-LF CAA test becomes positive for *S. haematobium* in the infant. Children who test *S. haematobium* positive will be treated with praziquantel according to Gabonese national treatment guidelines.

In addition, a customized questionnaire addressing the knowledge, attitude and practice (KAP) of schistosomiasis of mothers and infants will be asked. Health-related quality of life (HRQoL) will also be measured by using a standardized tool: this will allow filling a wide literature gap, where only very few studies have attempted to measure HRQoL in schistosomiasis endemic areas [43]. To our knowledge, this study will be the first one collecting information on HRQoL among pregnant women in areas endemic of schistosomiasis and of other parasitic infections such as malaria.

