### Recruitment of participants, data and sample collection

Prior to enrolment, the study will be explained to the pregnant women – and legal guardian if minor - presenting to the antenatal care centres (ANC) in Lambaréné (Albert Schweitzer and Regional Georges Rawiri Hospitals). Those willing to participate will be provided with the informed consent form (ICF) for signature for themselves and for their unborn child. Particular emphasis is given to information on *Schistosoma* transmission, diagnosis, associated pathologies and risk factors for *Schistosoma* infection in particular, and to intestinal helminths in general. Inclusion criteria are pregnancy at gestational age between 16 and 30 weeks (based on last date of menses), providing signed ICF, willing to deliver in one of the two maternities in the study areas and no plans to move out of the study area during the following 24 months. Exclusion criteria are reporting of complicated previous pregnancy, known chronic infections or diseases as HIV, HBV, HBC infections. Following the ICF process, a KAP questionnaire will be administered to collect standard demographic, health history, obstetrical data and information on schistosomiasis related knowledge, attitude and practice.. Economic and health-related quality of life (HRQoL) questionnaire will be included as well. The questionnaire will be used to measure HRQoL among all pregnant women at enrollment and to monitor HRQoL among the positive women over time. For this, the HRQoL questionnaire will be administered again to positive women 1 week after enrollment when test results are available and treatment provided (at A4) and a few months later, well after treatment completion (at C2). Physical examination will be done by the study physician; participants will be asked to provide urine (midstream urine will be collected in a clean container), stool and blood samples for parasite diagnostics and health care service. At delivery, newborns will be weighted, and gestation age will be recorded. The newborn’s anthropometry parameters, Apgar score at 1 and 5 min, maternal bleeding volume, placenta quality and weight will be collected. For details on study visits over time with respect to the study phases and details of sample collection see Additional file 1.

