### Additional outcomes

Maternal health outcomes, maternal anaemia (defined as Hb < 11 g/dl) at inclusion and at delivery will be investigated. In offspring, birthweight (with low birthweight defined as weight at birth < 2.5 kg) and small for gestational age (used as an indicator for possible intrauterine growth restriction) will be investigated. In addition, the exposure to PZQ during pregnancy will be evaluated in infants at the age of 12 and 24 months. Time to sit, crawl, stand and walk, incidence of illnesses and vaccine coverage during the follow-up will be recorded.

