## Trial status

Recruitment of study participants has started in April 2019 and is expected to be finished by April 2021: Follow-up of sub-study B is expected to be finished by July 2021 and of sub-Study C by the end of 2022.

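### The stated end of sub-study C (end of 2022) falls before infants born after December 2020 reach the 24-month evaluation of in-utero PZQ exposure

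*Protocol article*

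**What the plan says.** Four sections of the protocol article bear on this.

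- **Additional outcomes:** "the exposure to PZQ during pregnancy will be evaluated in infants at the age of 12 and 24 months". No restriction to early births is given.
- **Study design, sub-study C:** the sub-study "will follow up infants born to mothers included in sub-study A and their mothers for a maximum of 24 months", with N = 200.
- **Recruitment of participants, data and sample collection:** "Inclusion criteria are pregnancy at gestational age between 16 and 30 weeks".
- **Trial status:** "Recruitment of study participants has started in April 2019 and is expected to be finished by April 2021". The section then gives July 2021 as the projected close of sub-study B, and it puts the close of follow-up "of sub-Study C by the end of 2022".

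The exposed and control infants come from sub-study B (Study design), where at least 100 infected women are "randomised 3:1 (75:25) for immediate PZQ treatment during the pregnancy" or for treatment after delivery. The same section gives the control group a second role, as a safety control for the women and their offspring.

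**The concern.** The recruitment end, the gestational age at entry, the evaluation age and the study end are all printed in the same article, so they can be checked against each other. The time from April 2021 to the end of 2022 is about 20 months. It has to hold the rest of the pregnancy plus two years of the infant's life, and it does not.

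At stake is the longest-term offspring read-out in the only randomised comparison of PZQ exposure during pregnancy in this study. Its control side is small, about 25 women if 100 are randomised. The infants left out are set by calendar time. With concurrent randomisation this should not in itself favour either group, so the loss is mainly one of numbers and of an undelivered 24-month statement. A later report would also need a rule for infants under 24 months at study end, and the stated timeline gives none.

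**Working it through.** **Inputs**
- Recruitment: April 2019 to April 2021 (Trial status), taken as 1 April 2019 to 30 April 2021, which is 760 days.
- Gestational age at entry: 16 to 30 weeks (Recruitment section).
- Evaluation ages: 12 and 24 months (Additional outcomes).
- End of sub-study C: end of 2022, taken as 31 December 2022 (Trial status).
- Assumption: delivery at 40 weeks, so 10 to 24 weeks after entry.

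**Step 1: last births and their 24-month dates**

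Birth = enrolment + (40 − gestational age at entry) weeks.

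| Entry on 30 April 2021 at | Birth | Reaches 24 months | Age on 31 Dec 2022 |
|---|---|---|---|
| 30 weeks | 9 July 2021 | July 2023 | 17.7 months |
| 23 weeks | 27 Aug 2021 | Aug 2023 | 16.1 months |
| 16 weeks | 15 Oct 2021 | Oct 2023 | 14.5 months |

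Most lenient case: entry on 1 April 2021 at 30 weeks with delivery at 37 weeks gives birth on 20 May 2021 and 24 months on 20 May 2023. That is still 4.6 months after the end of 2022. The conflict for the last births therefore does not depend on the delivery week.

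**Step 2: latest enrolment that allows a 24-month visit**

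An infant must be born by 31 December 2020. Subtracting 24, 17 and 10 weeks gives enrolment by 16 July 2020 (entry at 16 weeks), 3 September 2020 (23 weeks) or 22 October 2020 (30 weeks). Recruitment continues for 288, 239 and 190 days after these dates.

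**Step 3: share affected, assuming uniform accrual**

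- Entry at 16 weeks: 288 / 760 = 38%.
- Entry at 23 weeks: 239 / 760 = 31%.
- Entry at 30 weeks: 190 / 760 = 25%.

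Taking the first or last day of April at either end of recruitment, and delivery at 37 to 42 weeks, widens the range to 19 to 41%.

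**Step 4: dependence on accrual**

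Let f be the fraction of the window after the cut-off. If the accrual rate falls linearly to zero, the share is f²: 0.25² = 6% to 0.379² = 14%. If it rises linearly from zero, the share is 1 − (1 − f)²: 1 − 0.75² = 44% to 1 − 0.621² = 61%.

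**Step 5: are women randomised that late?**

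Entry on 30 April 2021, plus about 1 week for test results, plus the 6-week maximum of urine follow-up, gives 18 June 2021. This fits the stated July 2021 end of sub-study B and suggests that randomisation continues to the end of recruitment.

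**The case against.** **The follow-up length is only a maximum.** For sub-study C, 24 months is an upper limit, and 200 places among 1000 mothers could be filled by early births. Under uniform accrual, 62 to 75% of women (about 620 to 750) deliver by December 2020, and for them the end of 2022 is enough. This stands for the incidence objective. A reader might infer that sub-study C as a whole cannot be completed, and the documents do not support that. The objection does not reach the PZQ-exposure evaluation, which is stated separately with a fixed age of 24 months.

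**The dates are projections.** Trial status says what is expected and is not a stopping rule. The evaluation is an additional outcome, not the primary objective of any sub-study. Both are true and keep the consequence moderate.

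**The July 2021 date is only suggestive.** If the 6-week series in controls were counted from their own treatment, 6 months after delivery, then 31 July 2021 less 6 weeks and 6 months is 19 December 2020. All sub-study B births would then fall early enough. That reading sits poorly with controls serving as the untreated comparison for CAA kinetics. It would also need randomisation to close months before recruitment, which the article does not say.

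**The size is not known.** A reader might take a quarter to two fifths as fact, or convert it to about 19 to 28 of 75 exposed and 6 to 9 of 25 control infants. Those figures need uniform accrual, all women at one gestational age, and exactly 100 randomised women. The article gives no accrual pattern and says at least 100.

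**How the 200 pairs are chosen.** A reader might also infer that unselected places would leave few exposed and control infants. The article is silent on selection, and a condensed article may leave that to the full protocol, so no finding rests on it.

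**Conclusion.** The point holds for infants born after December 2020. Entry at 16 to 30 weeks until April 2021, a 24-month evaluation without restriction, and an expected finish at the end of 2022 cannot all be met. The last infants would be about 14.5 to 17.7 months old at that finish, assuming 40-week delivery. The 12-month evaluation is feasible for every infant.

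That the conflict reaches randomised women rests on the inference that entry to sub-study B continues to the end of recruitment. The share affected is not given in the documents. It is about 25 to 38% under assumed uniform accrual (31% for entry at 23 weeks), about 6 to 14% if accrual declines linearly to zero, and about 44 to 61% if it rises linearly from zero. The point should be corrected, but it concerns an additional outcome and leaves the primary objectives untouched.

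**What to change.** Reconcile Study design, Recruitment, Additional outcomes and Trial status in one of two ways.

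1. **Extend the timeline.** Restate the end of follow-up as about October 2023 for infants of women randomised in sub-study B. The cost is some late visits and a later final database for this outcome.
2. **Keep the end of 2022.** State that the 24-month evaluation covers only births up to December 2020, and name 12 months as the age at which exposed and control infants are compared in full. The cost is a smaller 24-month sample, so the change is not free even though only text is altered.

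Either way, report by group how many infants could have reached 24 months by the end of follow-up, so that infants too young at study end are kept apart from those lost to follow-up.

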### Data safety and monitoring board

An independent data safety and monitoring board (DSMB) has been established which will review safety data in the sub-study B during the study.

### Sample size calculation

Analysis of the UCP-LF CAA (UCAA*hT*417) test performance will be compared against a composite diagnostic reference (i.e. by latent class analysis). Assuming a 10% egg positivity rate in the study population [32], about 1000 pregnant women should be tested to obtain 100 *Schistosoma* positive women. Assuming further a sensitivity of the index test (UCP-LF CAA) between 80 and 100% with 100 infected women, statistical precision (two-sided 95% confidence limit) of ±7.8% will be achieved if a sensitivity of 80% is observed and a lower limit of 96.4% if a sensitivity of 100% is observed. Due to the limited sensitivity of the egg detection test, to estimate the specificity, only study participants negative for reference tests should be included. Furthermore, assuming a true *Schistosoma* prevalence of 20% (based on a conservative estimate of 50% sensitivity of the egg test) and assuming a false positive rate of 20% of the other two reference tests (PCR and UCP-LF antibody test), at least 500 women will enter the naïve estimate of specificity. This will lead to a statistical precision of between ±3.5 and ± 4.3% depending on the observed specificity. For sub-study B, the analysis is based on the assumption of a non-inferiority delta of 0.10, identical probabilities of positivity and negativity at the end of the sub-study B for both tests (UCP-LF CAA and egg microscopy) and a discordance of 12%, with 100 pregnant women, the power will be 80% to show non-inferiority (type 1 error: 2.5% one-sided).

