The UCP-LF-CAA test is highly sensitive and specific and also performs well for urogenital schistosomiasis. Unfortunately, this test is not currently available as a point of care test. The assessment of this test in pregnant women in a *S. haematobium* endemic regions with weekly follow up of initially positive pregnant women as well as in infants to validate the CAA antigen test as an endpoint for measuring PZQ efficacy. Determining the true efficacy of PZQ against different *Schistosoma* infections is important for schistosomiasis control programs. It informs on the susceptibility of local *Schistosoma* infections towards PZQ as well as providing information for future efficacy trials for paediatric formulations of PZQ. Furthermore, using the UCP-LF-CAA test minimizes sample size in future efficacy trials as CAA levels are relatively constant in serum or urine, whereas the number of eggs is subjected to highly random daily fluctuations. The UCP-LF-CAA test clearly demonstrates that prevalence of active *Schistosoma* infections is underestimated by a factor of up to ten when compared to egg microscopy. Especially in low-endemic settings, the UCP-LF-CAA test is superior over parasitological methods. This test can easily identify individuals with very low levels of infection as well as early infections and is well-suited for determining efficacy (or even failure) of treatment. The test is ready to be taken up by industry for upscaling and deployment at large scale. So far, there is no alternative for evaluating long-term MDA programmes, and moving towards post-MDA surveillance or elimination.

Beyond the study, this work will prepare for the development of CAA rapid diagnostic tests, that can play a role in the future as a test-based schistosomiasis treatment strategy in pregnancy in endemic regions. Furthermore, the study tackles a neglected disease (schistosomiasis) and provides a concept to overcome the neglect of pregnant women and small children by schistosomiasis control programmes.

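### Sub-study B is sized only on a CAA-versus-microscopy non-inferiority test whose equal-positivity assumption conflicts with the protocol's own sensitivities, and its stated primary objective has no power or precision statement

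*Protocol article*

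**What the plan says.** All references are to the protocol article.

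- **Study design, sub-study B**, on purpose: "The primary objective is to determine the kinetics of CAA after treatment during pregnancy compared to the control group". Safety of praziquantel in pregnancy is the secondary objective. No non-inferiority objective is listed for this sub-study.
- **Same section**, on allocation: "women will be randomised 3:1 (75:25) for immediate PZQ treatment during the pregnancy". The other 25 are not treated during pregnancy. Women enter on a positive egg count, a positive CAA test, or both. Urine sampling stops once both tests are negative, and at six weeks at the latest.
- **Sample size calculation**, on sub-study B: a non-inferiority comparison with a margin of 0.10 at one-sided 2.5%, which rests on "identical probabilities of positivity and negativity at the end of the sub-study B for both tests (UCP-LF CAA and egg microscopy"). The claimed power is 80% in 100 women if the two tests disagree in 12% of them.
- **Same section**, on sub-study A: a true prevalence of 20%, "based on a conservative estimate of 50% sensitivity of the egg test", and a "sensitivity of the index test (UCP-LF CAA) between 80 and 100" per cent.
- **Discussion**: the prevalence of active "infections is underestimated by a factor of up to ten when compared to egg microscopy".

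The text does not say whether non-inferiority concerns positivity or negativity, nor whether the untreated women are in the comparison. The figure of 100 equals the whole of sub-study B.

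**The concern.** Two things do not fit together.

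First, the only sample size argument for sub-study B concerns a comparison of two tests within women. The primary objective is a comparison of CAA over time between two randomised groups. A reader cannot tell what 75 against 25 women can show on that objective.

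Second, the power statement needs both tests to be positive equally often at the end. Elsewhere the section treats microscopy as missing half of infections and CAA as missing at most a fifth. Wherever infected women remain, CAA should be positive more often, and a quarter of the cohort is untreated by design.

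At stake is what the result would mean. A failure on negativity might show only that CAA finds infections that microscopy misses. A success on positivity could follow from the same sensitivity gap, whatever treatment does. Neither would by itself support CAA as a measure of drug efficacy.

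**Working it through.** **Inputs from the document:** margin 0.10; discordance 12%; n = 100; one-sided 2.5%; egg sensitivity 50%; CAA sensitivity 80–100%; 75 treated and 25 untreated.

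**Assumptions added here:** untreated women remain infected; both tests have specificity 1 and are independent given infection; residual infection in treated women is varied, because no figure is given.

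**Formula.** Let d be CAA minus egg positivity and ψ the discordant proportion. For non-inferiority on negativity, power = Φ[(0.10 − d)/√((ψ − d²)/n) − 1.96]. For positivity, replace d by −d.

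**1. The stated figure.** With d = 0, ψ = 0.12, n = 100: 0.10/√(0.12/100) = 2.887, and Φ(2.887 − 1.96) = 82%. An exact Wald calculation gives 81.3% and an exact score test 75.4%. The stated 80% is reproduced.

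**2. What the sensitivities imply.** Among infected women with CAA sensitivity 80% and egg sensitivity 50%, CAA+/egg− is 0.80 × 0.50 = 40% and egg+/CAA− is 0.20 × 0.50 = 10%, a ratio of 4 to 1. The ratio rises with CAA sensitivity. Equality at 12% discordance needs 6% against 6%.

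**3. All 100 women.** The untreated women contribute d = 0.25 × (CAA sensitivity − 0.50) and ψ = 0.25 × 0.50 = 0.125. The first power column assumes that every treated woman is negative on both tests. The other two assume that treated women keep a balanced 12% discordance, so ψ = 0.75 × 0.12 + 0.125 = 0.215.

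| CAA sensitivity | d | Negativity, all treated clear | Negativity, balanced 12% in treated | Positivity, balanced 12% in treated |
|---|---|---|---|---|
| 80% | 0.075 | 10.8% | 7.9% | 96.9% |
| 90% | 0.100 | 2.5% | 2.5% | 99.3% |
| 100% | 0.125 | 0.3% | 0.6% | 99.9% |

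If all treated women clear, power on positivity is 99.9% or more. Exact score calculations with 0–10% residual infection in treated women give 0–9% on negativity.

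**4. Higher egg sensitivity (assumed), all 100 women, negativity.** CAA sensitivity is 80/90/100%.

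- Egg 70%: 68/41/16% if all treated clear; 42/22/9% with the balanced 12%.
- Egg 80%: 94/84/63% and 68/48/27%.

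**5. The 75 treated women only.**

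- Under the stated assumptions: 0.10/√(0.12/75) = 2.5, and Φ(2.5 − 1.96) = 71% (exact score 61%).
- With CAA 90%, egg 50% and residual infection r: d = 0.40r and ψ = 0.50r. Power on negativity is 99% at r = 5%, 66% at 10% and 8% at 20%.
- The normal approximation is generous when discordance is small. Over CAA 80–100%, the exact Wald test gives 88–95%, 48–74% and 5–26%; the exact score test gives 71–82%, 27–47% and 2–13%.

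**6. The primary objective.** For one between-arm contrast at two-sided 5% and 80% power, the detectable difference is 2.80 × √(1/75 + 1/25) = 0.65 SD, before any gain from baseline adjustment.

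**The case against.** The best defence has five parts.

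- **The arithmetic is right.** This stands; the issue is the assumption and its fit to the objective.
- **Direction and analysis set are details for an analysis plan.** This is fair as far as it goes, and their absence alone would not be a finding. But the article does fix n = 100, equality and 80%, and those figures can be tested against its own sensitivities.
- **The 50% is called conservative and belongs to sub-study A.** Sub-study B women are selected on a positive test, after three days of urine sampling with two readers per slide. The Discussion's factor of up to ten is a general remark on prevalence. This stands, and step 4 shows how much it matters.
- **Equality is assumed after treatment.** If nearly all treated women clear and only they are compared, the tests can nearly agree. This also stands, but that analysis has 75 women, not 100.
- **A comparison on positivity keeps its power, and validating CAA as an efficacy endpoint is a stated overall aim.** Both are true. Neither sizes the kinetics objective.

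A reader might infer that the non-inferiority test is almost bound to fail or trivial to pass. The document does not support that in general: it requires the untreated women in the comparison and an egg sensitivity near 50%. Nor is the discordance all in one direction, except at 100% CAA sensitivity.

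**Conclusion.** The point holds in limited form. The sample size for sub-study B does not address its stated primary objective, and its equal-positivity assumption cannot be reconciled with the sensitivities in the same section while untreated, infected women are among the 100.

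The size depends on the reading. With all 100 women and the document's sensitivities, power on negativity is about 0.3–11% and on positivity about 97% or more, given that untreated women stay infected. At an assumed egg sensitivity of 70–80%, power on negativity runs from about 9% to over 90%. With treated women only, it is about 71% under the stated assumptions, and otherwise follows residual infection, for which the document gives no value.

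No shortfall is shown for the kinetics comparison. Its precision is simply not stated.

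**What to change.** 1. **Restate the 80% figure.** Say whether non-inferiority concerns positivity or negativity and which women are compared, and use a discordance split that follows from the assumed sensitivities.
2. **Report CAA versus microscopy as a paired difference with a 95% CI** in treated women who were egg-positive at baseline, as description and not as proof that CAA is validated.
3. **Make the between-arm CAA comparison the primary analysis**, adjusted for baseline log CAA, and state its precision: 75 versus 25 gives 80% power for about 0.65 SD at two-sided 5%.
4. **Allow for how the data arise.** Values below the 2 pg/ml threshold and the end of sampling once both tests are negative leave early clearers without later measurements. A simple contrast at a fixed week would not cope with this; a censored mixed model or time to CAA negativity would be suitable.

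This changes protocol and analysis plan wording and needs no new patients. The price is giving up the 80% non-inferiority claim and some additional analysis work.

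### Sub-study B's 80% power counts all 100 women, but at the planned 75:25 allocation only 75 can show whether CAA tracks the response to PZQ

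*Protocol article*

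**What the plan says.** The Sample size calculation section of the protocol article powers sub-study B on a paired comparison of two tests in the same women. Its inputs are a "non-inferiority delta of 0.10"; as the assumed truth, "identical probabilities of positivity and negativity at the end of the sub-study B for both tests (UCP-LF CAA and egg microscopy"); for disagreement between the tests, "a discordance of 12" per cent; and a "type 1 error: 2.5% one-sided". It concludes that "with 100 pregnant women, the power will be 80% to show non-inferiority". The paragraph does not mention treatment arms and does not name an analysis set.

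The Study design section, under Sub-study B, sets enrolment at a minimum of 100 women found positive by egg microscopy, by CAA, or by both. They "will be randomised 3:1 (75:25) for immediate PZQ treatment during the pregnancy" or for delayed treatment. "The control group will not be treated during pregnancy"; these women are treated 6 months after delivery. Their stated roles are to show how CAA varies without treatment and to act as a safety control. Urine sampling stops when both tests are negative, or at the latest 6 weeks after PZQ.

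The Rationale and the Discussion give the purpose: to validate CAA as an endpoint for PZQ efficacy.

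**The concern.** The power statement uses one n for the whole sub-study, while the question it serves concerns response to a drug that a quarter of the women do not receive during pregnancy. Whether the two tests agree in an untreated woman says nothing about whether CAA falls to negative when worms are killed.

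Two things are at stake. If the comparison is made in treated women, the chance of showing non-inferiority may be well below the stated figure, and an inconclusive result would be read against a power that the design did not have. If the comparison is made in all 100 women, one paired proportion mixes treated and untreated results, and the assumptions behind the 80% no longer describe the data.

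**Working it through.** **Inputs.** From Sample size calculation: margin 0.10; true difference 0 (equal positivity on both tests); discordance 0.12; one-sided 2.5%, so z = 1.96; n = 100. From Study design, Sub-study B: 75 women treated immediately, 25 delayed.

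**Step 1: reproduce the stated figure.** For paired proportions with true difference 0, power = Φ(0.10/√(0.12/n) − 1.96).

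- n = 100: √(0.12/100) = 0.0346; 0.10/0.0346 = 2.887; Φ(2.887 − 1.96) = Φ(0.927) = 82.3%. Exact enumeration of the same Wald test gives 81.3%.
- n for 80%: (1.96 + 0.8416)² × 0.12/0.10² = 94.2, so 95 pairs.

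The stated 80% therefore fits a comparison in all 100 women, with about five to spare.

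**Step 2: the same calculation in the treated arm.**

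- n = 75: √(0.12/75) = 0.040; 0.10/0.040 = 2.50; Φ(2.50 − 1.96) = Φ(0.54) = 70.5%. Exact Wald enumeration gives 71.6%.
- Half-width of the 95% CI for the difference: 1.96 × 0.040 = 7.8 points.

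**Step 3: dependence on the discordance.** The protocol gives no separate rate for treated women. At n = 75 the normal formula gives:

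| Discordance | Power |
|---|---|
| 8% | 86% |
| 9% | 82% |
| 10% | 78% |
| 12% | 71% |
| 15% | 61% |

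The break-even for 80% is 75 × 0.10²/(1.96 + 0.8416)² = 0.75/7.849, or about 9.6%.

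**Step 4: can the 25 controls be pooled?** The sample-size section assumes an egg-test sensitivity of 50% and a CAA sensitivity of 80 to 100%. As a rough illustration that ignores selection at entry, apply these to infected women who stay untreated.

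- Positivity would differ between the tests by 30 to 50 points (80 − 50 to 100 − 50), not by zero.
- Discordance cannot be smaller than the difference in positivity, so it would be at least 30% in this arm, against the assumed 12%.
- In the pooled proportion the controls alone would contribute 25 × 0.30 = 7.5 to 25 × 0.50 = 12.5 women per 100, that is 7.5 to 12.5 points, against a margin of 10.

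The exact values would change with selection and repeat sampling. The conflict with equal positivity would remain.

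**Step 5: treated women needed for 80%.** 95 treated at 3:1 means 95/0.75 = 126.7, so about 127 randomised.

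**The case against.** A reader might infer that the sponsor made an arithmetic error. The documents do not support that: 80% is correct, and slightly cautious, for two tests applied to 100 women under the stated inputs.

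A reader might also infer that the design has 70% power as a matter of fact. That goes too far, for three reasons, all of which stand:

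- The sample-size paragraph does not restrict the comparison to treated women. That restriction follows from the stated purpose, not from an explicit analysis set.
- The 70% carries the 12% discordance over to treated women unchanged. If the arms differ, as Step 4 suggests, the treated-arm rate is unknown, and power could lie above or below 80%.
- One hundred is a minimum. With the assumed 20% prevalence and 80 to 100% CAA sensitivity, 1000 women would yield 160 to 200 CAA-positives. If all entered at 3:1, 120 to 150 would be treated, and power in treated women at 12% discordance would be 88 to 94%. Nothing guarantees that all would enter, and the stated power is tied to 100.

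It can further be said that untreated women are informative, because a good endpoint should stay positive without treatment. That is true, but it is a different question from agreement after treatment and is better answered by describing the control arm on its own.

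Finally, the sampling sentence could be read as collecting post-PZQ urine from controls too. The calendar does not allow this for all of them. Recruitment ends in April 2021 and sub-study B follow-up in July 2021, so a control enrolled last would not reach 6 months after delivery in time. Some early controls could, but the arm's stated role is to show CAA levels without treatment.

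Pooling does not remove the difficulty. With all 100 women the equal-positivity assumption fails; with 75 the stated n fails.

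**Conclusion.** The concern holds as a mismatch between the stated power and the analysis set. The 80% belongs to 100 pairs, and the planned 75:25 allocation supplies 75 pairs for the treatment-response question. With every other input kept, power is about 70%, so the chance of missing true non-inferiority is about 30% rather than 20%.

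This rests on three assumptions: that the comparison serves the stated aim of validating CAA as an efficacy endpoint; that 12% discordance holds in treated women (the range from 8% to 15% gives 86% to 61%); and that enrolment stops near the minimum of 100. No allowance for loss to follow-up is stated. The five spare pairs at n = 100 do not exist at n = 75.

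**What to change.** State that the paired non-inferiority comparison of CAA and egg microscopy is made in the immediate-treatment arm, and that the control arm's results on both tests are described separately. Then do one of the following:

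- restate the power at 75 treated women as about 70% if discordance is 12%, with the 8% and 15% values beside it; or
- replace the power by the expected 95% CI half-width of about 7.8 points.

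Since 100 is a minimum, add that the figure will be restated for the number actually treated. If 80% is to be kept at 12% discordance, about 95 treated women are needed, about 127 randomised at the present ratio; the existing minimum wording already allows this.

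Restating the power or the precision changes wording only. The price is a less favourable stated power. Keeping 80% costs about 27 more women than the minimum.
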